### Participant timeline

#### Sample size

A minimum of 2,000 participants who meet the inclusion criteria will be enrolled in the study. There will be up to 20 clusters, each comprising up to 150 to 200 households: 5 intervention clusters each in rural and peri-urban areas and 5 control clusters each in rural and peri-urban areas. The study is powered to detect at least a 20% between-group difference in HCV antibody self-testing, based on 80% statistical power and an alpha level of 0.05.

The survey of participants’ perceptions in relation to testing will include face-to-face interviews with 60 participants from each of the intervention and control groups. This is guided by empirical thinking, considering the feasibility with regards to the time and staff required to conduct the in-person interviews. The aim of these interviews is to further expand our understanding of preferences around HCV self-testing; there is no intention to set specific targets for measurement.

For the primary objective, the null hypothesis is that there is no significant difference in the proportion of individuals reporting HCV test results in the intervention versus control groups. The alternative hypothesis is that home delivery of HCV self-tests will significantly increase the proportion of individuals reporting HCV test results.

The study is not powered to detect significant differences in the secondary objectives. However, similar to the primary objective, the null hypothesis would be no significant difference between the intervention versus control groups. The alternative hypothesis would that home delivery of HCV self-tests will result in significantly higher numbers of HCV-infected individuals being diagnosed, linked to care and treated, making it a cost-effective approach to HCV case finding and elimination.

#### Assignment of interventions: allocation

Each member (neighbourhood block) of a matched cluster pair will be randomly allocated to the intervention or control group using a simple, computer-generated randomisation list. Each matched pair will be established based on similarities in type of geography (urban/peri-urban or rural), population size, sex distribution, age range, income and literacy. Within each UC and type of cluster (rural versus peri-urban), clusters will be put into pairs based on average household size (i.e. total estimated population in the cluster divided by the number of structures in the cluster). For example, the two rural clusters with the two largest average household sizes will be paired, followed by the next two rural clusters with the third and fourth largest average household sizes, and so on. Similar pairing will be performed for peri-urban clusters. If there are more than two clusters with the same average household size, then the estimated average age will be used as a tiebreaker, and pairs will be selected based on the closest estimated average age in those clusters. Once all clusters have been put into pairs, each member of a pair will be randomised to the intervention or control group.

For the face-to-face interviews, a subset of the main participants will be selected. Based on the study cluster assignment and testing results, study participants will be divided into the following eight subgroups:

Intervention group:In a rural cluster in the intervention group and completed a testIn a rural cluster in the intervention group, but did not complete a testIn a peri-urban cluster in the intervention group and completed a testIn a peri-urban cluster in the intervention group, but did not complete a test

Control group:In a rural cluster in the control group and completed a testIn a rural cluster in the control group, but did not complete a testIn a peri-urban cluster in the control group and completed a testIn a peri-urban cluster in the control group, but did not complete a test

For each subgroup, a randomly ordered list of participants will be generated via computerised randomisation. Then, for each subgroup, participants will be contacted by study staff in descending order on the list until a maximum of 15 individuals in each subgroup have completed the survey.

The trial is not blinded, and the participants and study staff know which group the participants are assigned to; therefore, no additional concealment mechanisms will be used.

### Data collection and management

All participant data relating to the study will be recorded in source documents and transcribed onto a paper case report form by the study team. The data will then be entered into OpenClinica Enterprise Edition, version 4.0, which is secure and password-protected.

Data for the results return interview (supplementary material, annex 1) will be collected over the phone. Data collection for the follow-up interviews among a subset of participants (supplementary material, annex 2) will be conducted face-to-face. Both the results return interview and the follow-up interview tools were created specifically for this study. Data relating to further HCV RNA testing and linkage to care will be extracted from records at Memon Goth Hospital and AKU treatment partners.

Costing information with regards to costs per test and costs per person diagnosed with HCV will be collected and analysed. The data collected will be used to conduct economic analyses that will include the following:The cost of delivering the HCV self-tests, including associated human resources timeThe cost of conducting an RDT at a local clinicThe number and type of diagnostic and therapeutic tests and proceduresThe number of healthcare facility visits before a diagnosis is made, or time to results

#### Confidentiality

Participants will be assigned a unique identifier, generated by FIND. Any participant records or datasets that are transferred to FIND will include this identifier only; no participant names or any other information that would make the participant identifiable will be transferred.

### Statistical methods

The data will be analysed using R version 4.1 or higher. A summary of statistical analyses that will be completed by the endpoint is shown in Table 2. The primary analysis will be performed using an intention-to-test analysis. The incentivisation methods described above will be employed to minimise missing data. The complete analysis plan is described in the study statistical analysis plan, which was drafted at the time the protocol was developed.

**Table 2 Tab2:** Statistical analyses to be completed by the endpoint

**Endpoint**	**Statistical analysis method**
1.1 The number and estimate of the proportion of participants who report completing HCV antibody testing in the intervention group 1.2 To assess whether the proportion of participants who report completing HCV antibody testing in the intervention group is greater than that of participants in the control group, by a margin of 20%	Test of proportions, comparing the proportion of individuals reporting HCV test results in the intervention versus control groups and between intervention groups
2.1 The number and estimate of the proportion of HCV antibody-positive individuals made aware of their status in the intervention versus the control group	Descriptive statistics; statistical tests comparing the number of individuals in the intervention versus the control group and between intervention groups
2.2 The number and estimate of the proportion of HCV antibody-positive individuals who are referred to and complete HCV RNA confirmatory testing in the intervention versus the control group	
2.3 The number and estimate of the proportion of HCV RNA-positive individuals who begin treatment in the intervention versus the control group	
2.4 Analysis of survey responses using proportions and means	Descriptive statistics for survey responses (e.g. proportions, means)
2.5 Cost per test completed and cost per person diagnosed (serology, RNA) in the intervention versus the control group	Ingredients-based cost calculation approach

The estimates of the study outcomes are proportions pfo,X, (fo = favourable outcome, X = element of {intervention, control}). They will be based on the definitions shown in Table 3, for estimation as well as for between-arm comparison.

**Table 3 Tab3:** Analysis table for primary and secondary analyses

Outcome							
		Favourable; test completed				Non-favourable; test not completed	Total
Test result and consequence 1		Positive and referred to further testing	Positive and not referred to further testing	negative	No result		
Test result and consequence 2		Positive and treated	Positive and not treated				
Study arm	Intervention	a	b	c	d	e	(a + b + c + d + e)
	Control	f	g	h	i	j	(f + g + h + i + j)
Total		(a + b + c + e + f + g + h + i)				(e + j)	total

The consequences (referred, treated) will be analysed independently of each other

The number and estimate of the proportion of participants who report completing HCV antibody testing in the intervention group will be calculated as:$$\mathrm{pfo},\mathrm{I }= (\mathrm{a}+\mathrm{b}+\mathrm{c}+\mathrm{d})/(\mathrm{a}+\mathrm{b}+\mathrm{c}+\mathrm{d}+\mathrm{e})$$$$\mathrm{pfo},\mathrm{C }= (\mathrm{f}+\mathrm{g}+\mathrm{h}+\mathrm{i})/(\mathrm{f}+\mathrm{g}+\mathrm{h}+\mathrm{i}+\mathrm{j})$$

The absolute and relative proportions will be calculated separately by arm (all arms) and reported with their two-sided 95% Wilson score confidence interval.

The difference pfo,I—pfo,C will be assessed using a one-sided test with a margin of 20%, by applying the following hypothesis:$$\mathrm{H}0:\mathrm{ pfo},\mathrm{I }-\mathrm{ pfo},\mathrm{C }\le 20\mathrm{\%}$$$$\mathrm{HA}:\mathrm{ pfo},\mathrm{I }-\mathrm{ pfo},\mathrm{C }> 20\mathrm{\%}$$

The difference of the proportions in the intervention and control arms will be reported, together with its confidence interval (see below) and the *p*-value related to the null hypothesis mentioned above.

The alpha level for the analysis will be set at 0.025 (1 one-sided test with an alpha level of 0.025).

The difference and its confidence interval will be estimated using a generalised binary mixed logit model with “cluster pair” as a random effect and “group” as a fixed effect (e.g. using the R function “lmer”). The two-sided 95% asymptotic confidence interval will be used to derive the one-sided lower 97.5% confidence limit, which will be used for interpretation. In addition, the odds ratio and its confidence interval will be reported.

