## Methods/design

### Design

This is a parallel group, non-blinded, cluster randomised superiority trial comparing the secondary distribution of HCV self-tests with the secondary distribution of information pamphlets encouraging individuals to visit a testing facility for HCV screening. A subset of participants (*n* = 120) from both the intervention and control groups will be asked to participate in face-to-face interviews regarding their perceptions of the testing experience, to provide insights into the acceptability and feasibility of HCV self-testing. The study timeline is shown in Table 1.

**Table 1 Tab1:** Study timeline

	**Enrolment**	**Follow-up for all participants**	**Follow-up for HCV antibody-positive participants**
**Procedure**	**Day 1**	**Months 1–2**	**Months 1–8**
Inclusion and exclusion criteria	X		
Informed consent obtained	X		
HCV antibody testing (either HCV self-test left with the household or participants in the control group attend Memon Goth Hospital)	X	X	
Collection of test results and survey of perceptions of the testing process		X	
Referral of HCV antibody-positive individuals for confirmatory testing and linkage to care		X	X
Linking of data for the RDT (control group) and RNA test and treatment initiation (as applicable for the intervention and control groups)		X	X
Adverse event (AE)/serious adverse event (SAE) review	X	X	X
Cost data collection and analysis	X	X	X

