### Study setting

The study will take place in the Malir district of Karachi, Pakistan. Darsano Chano (UC9) is in a rural area and has a population of approximately 10,000 individuals. Malh (UC10) is peri-urban and has a total population of approximately 50,000 individuals. Both UCs have small, well-established community clinics, which have formed the hub of the larger ongoing HCV micro-elimination programme. UC9 and UC10 have approximately 2,000 and 10,000 households, respectively, with an average of five family members per household.

The study will take place at the homes of eligible adults visited by study staff. Based on the current micro-elimination programme, an estimated 7,500 participants remain in both UC9 and UC10 who have not yet been tested as part of the larger micro-elimination programme. Each UC has been subdivided into ten blocks/clusters, based on neighbourhood geography, as shown in Figs. 1 and 2; these clusters have not yet been randomised, but will be matched-pair randomised on a 1:1 basis.

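### The per-arm Wilson intervals ignore cluster randomisation, Table 2's test does not match the model in the text, and that model with a pair effect only does not account for the randomised clusters either

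*Protocol article*

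**What the plan says.** The Design section states: "This is a parallel group, non-blinded, cluster randomised superiority trial". Under Study setting, the clusters "will be matched-pair randomised on a 1:1 basis". The Sample size section adds "A minimum of 2,000 participants who meet the inclusion criteria will be enrolled in the study" and "There will be up to 20 clusters, each comprising up to 150 to 200 households", split into ten intervention and ten control clusters.

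The Statistical methods section then names methods in three places:

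- **Table 2**, introduced as a summary, gives for the primary endpoints (1.1 and 1.2) a "Test of proportions, comparing the proportion of individuals reporting HCV test results in the intervention versus control groups". For the secondary endpoints 2.1 to 2.3 it gives descriptive statistics and unspecified statistical tests. Clustering is not mentioned.
- **Text after Table 3, per-arm estimates:** the proportions in each arm are to be "reported with their two-sided 95% Wilson score confidence interval".
- **Text after Table 3, comparison:** the difference and its interval come from a mixed logit model with cluster pair as the random effect and group as the fixed effect. Its lower 97.5% limit is the basis for interpretation. A p-value for the 20% margin hypothesis is also promised, but the text does not say which test produces it.

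**The concern.** A Wilson score interval and an ordinary test of proportions take their standard error from the number of people. In this design the units randomised are neighbourhood blocks. People in one block are likely to resemble each other in distance to the hospital, literacy and willingness to test, so 1,000 people in ten blocks carry less information than 1,000 independent people.

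Two things are at stake. Uptake in each arm, which programmes are likely to quote, would appear with false precision. And the primary endpoint has a test in Table 2 and a model in the text, with the p-value assigned to neither, so a p-value and a confidence limit from different methods could point to different conclusions.

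**Working it through.** **Inputs.** From the Sample size section: 2,000 participants and 20 clusters, hence 1,000 people and 10 clusters per arm and m = 2,000/20 = 100 per cluster. From Statistical methods: one-sided alpha 0.025. Assumed, because the document gives neither: ICC from 0.01 to 0.10, and 70% uptake for the illustration.

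**The plan's own figure.** The minimum of 2,000 cannot be reproduced, because no control proportion or ICC is stated. With independent participants, a 20-point difference at 80% power and two-sided 5% needs 164 people in total at a control proportion of 20%, or 194 at 40%. If 2,000 was meant to give exactly 80% power against zero difference, the implied design effect is 2,000/164 = 12.2 or 2,000/194 = 10.3, an ICC of (12.2 − 1)/99 = 0.11 or (10.3 − 1)/99 = 0.09. This back-calculation only shows that the assumed range is not extreme.

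**Step 1, per-arm interval.** Wilson for 700/1,000 runs from 0.671 to 0.728, a half-width of 2.8 points. Design effect DE = 1 + 99 × ICC. Clustered half-width = multiplier × √(0.7 × 0.3/1,000 × DE), where √(0.21/1,000) = 0.01449. The multiplier is 2.262 (t with 9 degrees of freedom, for ten clusters) or 1.96 (normal). Approximate coverage of the nominal 95% Wilson interval = 2Φ(1.96/√DE) − 1.

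| Assumed ICC | DE | Half-width, t (points) | Half-width, normal (points) | Wilson coverage |
|---|---|---|---|---|
| 0.01 | 1.99 | 4.6 | 4.0 | 84% |
| 0.02 | 2.98 | 5.7 | 4.9 | 74% |
| 0.05 | 5.95 | 8.0 | 6.9 | 58% |
| 0.10 | 10.9 | 10.8 | 9.4 | 45% |

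At ICC 0 the t version gives 2.262 × 0.01449 = 3.3 points, so about 0.5 points of excess over Wilson at that end comes from the multiplier alone. The normal column isolates the design effect. Matching does not rescue a single arm's interval: simulated Wilson coverage at ICC 0.05 was 61% with no variance shared within pairs and 60% with half shared.

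**Step 2, an unadjusted test.** Ignoring matching, actual one-sided error = 1 − Φ(1.96/√DE): 0.082 at ICC 0.01, 0.128 at 0.02, 0.211 at 0.05 and 0.276 at 0.10.

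**Step 3, the model in the text.** Each pair holds one intervention and one control cluster. A pair intercept is common to both and cancels from their difference. What remains is binomial variation plus the variance between the two clusters of a pair, and the model has no term for the latter. The standard error of the group effect is therefore close to that of the unadjusted test. A simulation checked this: 10 pairs, 100 people per cluster, 40% uptake in both arms, a null of no difference, 1,000 runs per setting. One-sided error at nominal 0.025:

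| ICC | Variance shared within pairs | Unadjusted test | Pair-only mixed logit | Paired t on cluster proportions |
|---|---|---|---|---|
| 0.01 | none | 0.064 | 0.064 | 0.022 |
| 0.05 | none | 0.188 | 0.190 | 0.018 |
| 0.05 | half | 0.143 | 0.147 | 0.032 |
| 0.10 | none | 0.247 | 0.250 | 0.024 |
| 0.10 | half | 0.205 | 0.207 | 0.030 |

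The simulation tests a null of zero rather than the 20-point margin. The argument about the omitted variance is the same for both.

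**The case against.** The strongest objection is that Table 2 is introduced as a summary, that the full analysis plan is a separate document, and that the text bases interpretation on the model's lower limit. This stands as far as the p-value goes. A reader might infer that the reported p-values are far too optimistic, or that two rival primary tests are prespecified. The document does not support either: Table 2 may be loose shorthand, and the p-value may come from the mixed model. How optimistic an unadjusted p-value would be also depends on an ICC that is not given and on the gain from matching. The standard error is understated 1.2-fold at ICC 0.005 and 3.3-fold at 0.10.

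A reader might equally infer that the mixed model is the analysis that respects the design, so that only the label in Table 2 needs correcting. Step 3 shows otherwise.

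Two smaller objections also stand. The Wilson intervals are descriptive and do not drive the primary decision. And unspecified tests for the secondary endpoints do not commit the plan to assuming independence. Those denominators are sparse: if the 5% general-population prevalence in the Background applied (an assumption), 2,000 participants would include about 100 people with HCV, or five per cluster.

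None of this changes the first point. The Wilson intervals are a specific choice made in the main text, and a summary table should not name a different method from the text that it summarises.

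**Conclusion.** Three statements hold.

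- The per-arm Wilson intervals are too narrow for any positive ICC. The direction needs no assumption. The size, 2.8 points against 4.6 to 10.8 for ICCs of 0.01 to 0.10, rests on assumed ICCs, equal clusters of 100 and 70% uptake, and includes the t multiplier.
- Table 2 and the text name different methods for the primary endpoint, and the source of the p-value is open. Only if it came from an unadjusted test would one-sided error be about 8% at ICC 0.01 (6.4% in simulation) and about 14 to 21% at ICC 0.05, depending on the gain from matching.
- Adopting the model as written in both places would not cure this, because a pair effect alone leaves out the between-cluster variance within pairs. This matters most, since the limit used for interpretation comes from that model.

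The correction should be made; it needs no new data.

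**What to change.** 1. Choose one primary analysis that accounts for the randomised clusters, and take both the lower confidence limit and the p-value from it. One option is a paired cluster-level analysis: the mean of the ten within-pair differences in proportions, compared with the 20-point margin using t with 9 degrees of freedom. The other is a mixed model with a random effect for cluster in addition to pair, with a small-sample correction for 20 clusters.
2. State that analysis in the text of Statistical methods and in Table 2. Changing Table 2 alone would leave the pair-only model in place.
3. Replace the Wilson intervals by t-intervals on the ten cluster proportions in each arm, or by Wilson intervals on the effective sample size n/DE.
4. Keep the sparse secondary endpoints descriptive, or use a cluster-robust method where the counts allow. A cluster-level proportion may be undefined where a cluster has no antibody-positive or RNA-positive participants.

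The cost is wording in the protocol and the analysis plan, wider reported intervals and less favourable p-values. Data collection does not change.

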### Study aim and objectives

This study aims to evaluate the acceptability and impact of the secondary distribution of HCV self-tests in the context of a house-to-house HCV micro-elimination programme in Malir district, Karachi division, Pakistan. The primary objective is to assess the impact of HCV self-testing on HCV antibody testing rates. The secondary objectives are to assess the impact of HCV self-testing on linkage to and completion of HCV RNA confirmatory testing in HCV antibody-positive individuals and treatment initiation in HCV RNA-positive individuals eligible to begin treatment; to assess the acceptability and feasibility of HCV self-testing; and to assess the cost and cost-effectiveness of HCV self-testing compared with facility-based testing.

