**Fig. 3 Fig3:**
[figure not shown]
Trial flow diagram

In the control group, if the participant(s) are not at home, the study staff will leave information about HCV testing and direct them to the nearest clinic that offers HCV testing services; the participant(s) will not be left an HCV self-test. Study staff will however leave a mobile phone number for the participant(s) to call if they need further information on HCV testing.

In both groups, if no-one is at home or no one aged 18 years or more is present, the study staff will make as many return visits as necessary to contact a household member.

A small incentive, comprising a 500 rupee (approximately 3 USD) phone credit voucher, will be provided to participants in both the intervention and control groups for any information they return via a phone call, including whether they took the test and, if so, what the result was. During this return phone call, the study team will follow up with the participant to inquire whether they completed the test, record any test results, and conduct a brief interview.

For all participants who report a positive HCV antibody test, study staff will make an appointment to return to their house to enrol them in the larger micro-elimination programme. During this home visit, they will complete a blood draw for HCV viraemia testing and APRI (aspartate aminotransferase to platelet ratio index) liver staging, to be performed at Memon Goth Hospital. The viraemia testing will be performed using an HCV core antigen assay (ARCHITECT HCV Ag assay, Abbott® Diagnostics). If a participant’s result is in the grey zone (≥ 3 to ≤ 10 fmol), a second sample from the same participant will be tested for HCV RNA (Xpert HCV Viral Load, GeneXpert® IV, Cepheid, France) to determine viraemia. If the participant is viraemic, further care and treatment will be provided to their doorstep. All participants who report a negative HCV antibody test will be encouraged to seek a retest, as per the national guidance.

Approximately 1 month following the start of enrolment, face-to-face interviews will be conducted with a subset of participants in both the intervention and control groups, to explore their perceptions of the testing process.

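### Table 3 has no cell for confirmatory-test completion or viraemia, so it cannot yield secondary endpoints 2.2 and 2.3 as the protocol defines them

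*Protocol article*

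**What the plan says.** The Outcomes section and Table 2 (endpoints 2.2 and 2.3) agree on two secondary outcomes. Endpoint 2.2 concerns antibody-positive people who are both referred for confirmatory testing and complete it. Endpoint 2.3 is "The number and estimate of the proportion of HCV RNA-positive individuals who begin treatment". The Study aim and objectives section words the treatment objective more narrowly: "treatment initiation in HCV RNA-positive individuals eligible to begin treatment".

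The text after Table 2 then introduces the outcome proportions and says: "They will be based on the definitions shown in Table 3, for estimation as well as for between-arm comparison". The caption of Table 3 is "Analysis table for primary and secondary analyses". Within the column for completed tests, the first consequence row has "Positive and referred to further testing" and "Positive and not referred to further testing". The second row sits over the same cells (a and b for intervention, f and g for control) and splits them into "Positive and treated" and its complement. The note under the table names referral and treatment as the two consequences, each to be analysed without regard to the other.

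On procedure, the Trial processes and intervention section states: "For all participants who report a positive HCV antibody test, study staff will make an appointment to return to their house". It provides treatment to those found viraemic. The Study setting section says that control participants with a positive rapid test have blood drawn at the hospital straight away.

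**The concern.** The table named as the basis for estimation holds neither of the two facts that these endpoints need: whether the confirmatory test was done, and whether it showed viraemia.

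A confirmation measure taken from the table would be a process step that staff plan to carry out for every reported positive. Loss between the appointment and the blood draw would not show. The arms could differ at exactly that step, because controls are bled on the spot at the hospital while self-testers wait for a home visit. Linkage to confirmatory testing and its completion form a stated secondary objective.

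A treatment measure taken from the table would count antibody-positive people without viraemia as not treated. It would then move with each arm's viraemic share and confirmation rate, as well as with treatment uptake.

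**Working it through.** The document gives no value for either secondary proportion, so there is no figure to reproduce. The check sets the cells of Table 3 against the definitions. Viraemic here means positive on the protocol's viraemia pathway, which endpoint 2.3 calls HCV RNA-positive.

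**Step 1: what each source can deliver**

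| Endpoint | Definition (Outcomes, Table 2) | Only ratio among positives that Table 3 allows |
|---|---|---|
| 2.2 | referred and test completed / antibody-positive | a/(a+b) in row 1 = referred / antibody-positive |
| 2.3 | treated / RNA-positive | a/(a+b) in row 2 = treated / antibody-positive |

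The control arm has f/(f+g) in the same way. The protocol does not print these ratios; they are what the cells permit.

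**Step 2: can row 2 be read as RNA-positive?** No. Antibody-positive people without viraemia would then have no cell, and the printed arm total a+b+c+d+e would no longer account for everyone.

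**Step 3: size, confirmation.** Take 100 antibody-positives, all referred as planned. Completion is not given, so assume 60–100%. The Table 3 ratio is 100/100 = 100% throughout, while the defined outcome runs from 60% to 100%. If 5% were not referred, the ratio would be 95% and the defined outcome 0.95 × 60% = 57% to 0.95 × 100% = 95%.

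**Step 4: size, treatment.** With full referral, the Table 3 ratio equals completion × viraemic share × uptake among the viraemic. None of these is given, so all are assumed.

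- Completion 100%, viraemic 50%, uptake 90%: 1.00 × 0.50 × 0.90 = 45%
- Completion 100%, viraemic 75%, uptake 90%: 1.00 × 0.75 × 0.90 = 67.5%, about 68%
- Completion 80%, viraemic 65%, uptake 90%: 0.80 × 0.65 × 0.90 = 46.8%

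The defined outcome is 90% in all three. Over wider assumed ranges (completion 60–100%, viraemic 50–80%, uptake 70–90%), the Table 3 ratio runs from 0.60 × 0.50 × 0.70 = 21% to 1.00 × 0.80 × 0.90 = 72%, against 70–90% as defined.

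**Step 5: are the denominators different on the protocol's own figures?** Study setting gives sensitivity 98.1% and specificity 99.6% for the professional-use version of the self-test. Taking the 5% general-population figure as antibody prevalence (an assumption), each 100 people tested give 5 × 0.981 = 4.905 true and 95 × 0.004 = 0.38 false positives. So 0.38/(4.905 + 0.38) = about 7% of positives would be false, before counting true antibody-positives who are not viraemic.

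**The case against.** The strongest reply is that the protocol prints no secondary estimator. Formulas are given only for the primary outcome, and the proportions tied to Table 3 are labelled as favourable outcomes, which the table equates with a completed test. The Outcomes section and Table 2 state endpoints 2.2 and 2.3 consistently, and an analyst could simply follow them. The full analysis plan is elsewhere and may do so. Data on RNA testing and linkage to care will be extracted in any case (Data collection and management), so nothing is lost for good. The study is also not powered for these outcomes (Sample size).

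Most of this stands and limits the point. It does not remove the contradiction. The caption extends Table 3 to the secondary analyses, and the note beneath it names referral and treatment as what is analysed. For 2.2 and 2.3, Table 2 offers only descriptive statistics and unnamed tests, so it does not settle which definition governs.

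A reader might go further and infer that the trial will report a confirmation rate near 100% that cannot differ between arms. The document does not support that. The appointment for every reported positive is an intended procedure, not a recorded result, and Table 3 itself provides cells for positives who are not referred. Little room to differ is as far as the text goes.

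**Conclusion.** The point holds as an internal contradiction. Table 3 cannot yield endpoints 2.2 and 2.3 as the Outcomes section and Table 2 define them. Taken from the table, the first becomes referral instead of completion, and the second takes all antibody-positives as its denominator instead of RNA-positives. The illustrative gap of 45–68% against 90% rests wholly on the assumed viraemic share and uptake, with everyone confirmed; incomplete confirmation would widen it.

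It would be wrong to conclude that incorrect rates will be reported, since the analysis plan may define both endpoints properly. If it does, Table 3 still needs correcting to match. The primary outcome formulas are untouched and only unpowered secondary outcomes are affected, so this should be corrected but does not threaten the main result.

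**What to change.** - In Table 3, replace the referral split among antibody-positives with viraemia test completed or not completed.
- Split those completed into viraemic and not viraemic, and place treated or not treated within the viraemic only.
- Print the numerator and denominator of 2.2 and 2.3 beside the primary formulas, matching the Outcomes section.
- Reconcile the eligibility wording in Study aim and objectives with the RNA-positive denominator in Outcomes, so that one denominator is stated for treatment start.
- Keep referral as a descriptive count by arm.

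The cost is an edit to one table and to the matching shells in the analysis plan. The data on confirmatory testing and treatment initiation are already to be extracted and linked for both arms (Data collection and management, Table 1). No trial procedure changes.
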